**Fig. 2 Fig2:**
[figure not shown]
Flowchart of the interventions, including a web-based Health Risk Assessment (HRA) with tailored advice and suggestions of choices, and motivational interviewing

For the participants in both intervention arms, follow-up questionnaires are conducted after 6 and 12 months, but without any tailored advice as feedback. In case of non-response to a questionnaire after two weeks, an automatic electronic reminder is sent to the employee. After another two weeks without response, the employee is contacted by a member of the research team reminding him/her to fill out the questionnaire and/or to provide assistance if needed.

### Limited (control) intervention

The limited health intervention program consists of the following elements:a web-based HRA (described above), including tailored and personalized advice for health behavior change, with a suggestion of choice out of three “usual care” health promotion activities for every identified risk factor. This is followed by usual care, according to Dutch OP guidelines [41].an electronic newsletter of approximately two pages, sent every three months. The newsletter includes general information on PerfectFit and on a healthy lifestyle.

### Extensive intervention

In the extensive intervention group, the limited intervention program is extended with personalized MI sessions with an OP, together with additional tailoring based on motivational elements in the web-based HRA and an additional motivational paragraph in the newsletters.

MI is conducted in the form of individual coaching sessions run by trained OPs. Altogether, they include seven motivational coaching sessions: three face-to-face sessions (30–45 min per contact) and four telephone contacts (15–30 min per contact) [42]. The MI training for OPs was organized as a continuous medical education (CME) session and after successful completion of the training OPs received credits. The training was free of charge and it consisted of three full days of group training by a certified MI trainer with 3 follow-up coaching sessions of 4 hours each [43]. During the training, OPs became familiar with the basic principles of MI and they practiced techniques needed for conducting MI. The aim was to elicit long-term healthy behavior in the participants.

To assure and maintain a high level of quality of MI during the intervention period, we conducted two quality assurance activities [44]. First, after every three months, each OP was asked to audio record the first face-to-face consultation with a participant, using a voice recorder. Recorded sessions were transcribed verbatim and analyzed using the validated Motivational Interviewing Treatment Integrity code (MITI) for the presence of core elements of the MI technique, such as reflexivity, open-questioning, and empathy [45, 46]. Scorings were done by the first author and a co-investigator in this study, who are both experienced MI-coaches and familiar with the scoring technique. Within a month after the recordings, the OPs received feedback on the quality of their MI-techniques. Second, after every MI session with participants, OPs had to fill out a form related to the MI session with a participant, such as if it was a face-to-face or telephone session, the amount of time it took, and what stage of change the participant was in (5 stages, ranging from pre-contemplation to maintenance).

The online advice within the HRA additionally includes tailoring based on motivational aspects such as intention to change and personal preferences, and it includes three more suggestions of choice for health promotion activities. In contrast to usual care, these additional suggestions of choice include e-health interventions, fitness centers with national coverage, and the use of an activity tracker (accelerometer). The accelerometer is offered for free and is primarily aimed at providing “biofeedback” to those participants who are physically inactive and who are motivated to improve their level of physical activity by using this small monitoring device during twelve consecutive weeks [47].

### Outcome measures

The following outcome measures will be taken into account:**Primary outcome measure:**

General health

At baseline, 6 months and 12 months, we measure (d) general health using the first question of the Short Form 36 Health Survey (SF-36) [48] (‘Overall, how would you rate your health?’), which has five possible answers, ranging from ‘poor’ to ‘excellent’.**Secondary outcome measures:**

Quality of life

Quality of life and its utility values will be calculated using the EuroQol 5 dimensions self-report questionnaire (EQ-5D) [49] and two domains from the SF-36 (physical functioning and vitality) [48]. The EQ-5D is a health status classification system consisting of five dimensions: mobility, self-care, usual activities, pain/discomfort, and anxiety/depression. We distinguish three levels for each dimension: no problems, moderate problems, and extreme problems. Within the SF-36, 4 questions are asked for physical functioning with 5 answering options, ranging from “totally agree” to “totally disagree”. For vitality 4 questions are asked with 6 answering options ranging from “all the time” to “never”.

#### CVD-risk score

CVD-risk will be estimated at baseline and after 12 months, using the European SCORE function (EuroSCORE), the Framingham Risk Score (FRS), and the QRISK2. The EuroSCORE [35, 50] estimates the 10-year risk for total fatal CVD-risk, based on age, sex, smoking, blood pressure, and total cholesterol. The FRS estimates the 10-year risk for CVD mortality and morbidity by adding hypertension treatment status, HDL-cholesterol, and diabetes status [36, 51, 52]. The QRISK2 [28] estimates the risk of CVD by adding ethnicity, diabetes, family history for angina or heart attack, chronic kidney disease, atrial fibrillation, blood pressure treatment, rheumatoid arthritis, cholesterol/HDL ratio, and body mass index.

#### Obesity

Obesity, measured with waist circumference (in cm) and Body Mass Index (BMI,kg/m2), was determined at baseline and will be repeated at 12 month follow-up.

#### Lifestyle

At baseline and after 6 and 12 months, current behavior is assessed for smoking, physical activity, alcohol consumption, and nutrition, measured as adherence to Dutch public health guidelines (yes/no), i.e., not smoking [53], being moderately physically active for 30 min on at least 5 days a week [54], not drinking more than 1 (women) or 2 (men) glasses of alcohol a day [55], eating at least 200 g of vegetables per day [55], and eating at least 2 pieces of fruit per day [55] .

At baseline, self-reported intentions to change behavior targeting smoking, physical activity, alcohol, dietary behavior or body weight will be assessed. For smoking, intentions to change are measured using dichotomous response scales (yes/no). For the other lifestyle items, the answering options are dichotomized into ‘I will start this month; I will start within 6 months; I will start, but I don’t know when’ and ‘I would like to, but I don’t have enough time; I would like to, but I can’t because of a disease, a disability or a doctor advised me not to; other’.

After 6 months, actual lifestyle behavior change will be measured by the number and type of health promotion activities they choose to participate in, within the 6 months after baseline (participants’ responsiveness to the intervention). Also the chosen mode of delivery (provided by employer or not) will be assessed.

#### Work ability

Work ability will be measured at baseline, 6 months and 12 months, using the Work Ability Index (WAI) questionnaire [56], which consists of seven dimensions: an individual’s (i) physical and (ii) mental demands related to work, (iii) diagnosed diseases, (iv) experienced work limitations due to disease, (v) sick leave in the previous 12 months, (vi) work ability prognosis, and (vii) mental resources. The WAI index is derived as the sum score of the ratings on each dimension. The range of the summative index is 7–49, which is categorized into “poor” (7–27), “moderate” (28–36), “good” (37–43), and “excellent” (44–49) work ability [57].

#### Productivity at work

Productivity at work and, if applicable, the reason for any self-reported loss in productivity was measured at baseline and will be repeated after 12 months. We use the Quantity and Quality (QQ) method [58], which is derived from the PRODISQ [59, 60]. On 10-point numerical scales, participants are asked how much work they performed during regular hours on their last regular workday and what the quantity of the work was compared to normal.

We also quantify to what degree employees are present at work but limited in their job performance due to any health problems, by using the short version of the Work Limitations Questionnaire (WLQ-8) [61–63]. The WLQ-8 consists of four dimensions: physical demands (2 items), time management (2 items), mental-interpersonal demands (2 items), and output demands (2 item). Individuals are asked to base their responses on their previous two weeks of work and to rate impairment on a 5-point scale ranging from “always” to “never” with an additional response item “does not apply to my job”.

### Process evaluation

After the intervention period, several process characteristics will be evaluated using the RE-AIM model [64, 65], which consists of the following five elements:Reach (eligibility, number of cardio screenings, percentages of inclusions and exclusions, individuals’ characteristics, and compliance and determinants of the participants to the screening, HRA, MI-counselling sessions, and 6 and 12 months follow-up measurements);Effectiveness (outcomes at 6 and 12 months);Adoption (characteristics of OPs and clusters);Implementation (amount, duration, timing and quality of MI-counselling sessions, satisfaction of participants with the sessions ); andMaintenance (long-term implementation).

Participants’ opinions of the perceived usefulness of the web-based HRA, of the coaching, and of the impact on their lifestyle change will be evaluated at six months, on a 5-points Likert scale (from 1 = strongly disagree to 5 = strongly disagree). Participants’ satisfaction with the OP will also be measured at six months, using standard questions based on the PSOHQ [66] .

### Sample size and power calculation

The primary outcome measure in this study is general health. Based on a study of more than 4000 asymptomatic Dutch individuals [67], we assumed that the average value for general health score measured by the SF-36 within our target study population is 71 (SD 19, scale 0–100). Based on an intervention study that assessed general health, albeit with a less intensive intervention [68], we assume a relevant difference in the general health score between the intervention and control groups after 12 months of 10 % in favor of the intervention group. With a power of 80 %, a significance level of 5 %, two-tailed testing, a compensation for cluster randomization with an estimated intra-cluster correlation coefficient of 0.05, the assumption of similar groups, and with the intention of demonstrating superiority, approximately 220 participants per group are needed to demonstrate a difference in treatment effect of 10 % between the two groups. With an expected participation of 50 % (based on previous studies of health interventions for military personnel) and a loss to follow-up of 30 %, the RCT required inviting 2 × 634 individuals, so 1268 in total.

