## Methods

### Study design

The PerfectFit study is a cluster randomized control trial [29] (cRCT) among employees of three organizations, aimed to compare two groups: a purely internet-based approach (*limited or control* intervention) and a group that is exposed to the internet-based approach supplemented with MI (“the blended approach”, *extensive* intervention). The internet approach consists of a web-based HRA (later addressed as “HRA“) with tailored and personalized advice for health behavior change as well as pros and cons of the options for change. In the extensive intervention, the HRA is supplemented with face-to-face care provided by an (in-house) occupational physician (OP) using MI. The elements of the intervention are based on existing modules, previously evaluated RCTs [22, 30–32] and a recent meta-analysis [33]. Measurements were done at baseline and will be repeated after 6 and after 12 months.

Participants were included between 2012 and 2014 after providing written informed consent. There were no risks associated with participating in PerfectFit. Confidentiality was guaranteed during the study for all participants, as no information about the cardiovascular risk profiling, the HRA, or the coaching was provided to others than stated in the Participant Information Form. Ethical approval was obtained from the Medical Ethical Committee of Erasmus MC Rotterdam (METC) by registration number MEC 2012–459. The trial was registered on November 14^th^ of 2014 at the Netherlands Trial Register by registration number NTR4894.

After trial commencement, three OPs withdrew because of other priorities in work or due to personal issues, resulting in the loss of one military cluster and less inclusions than expected. In order to achieve sufficient power, we obtained approval of the METC to include an additional organization (i.e., an academic hospital).

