### Randomization, blinding, and allocation to interventions

Military bases, regional police forces, and hospital wards were randomly assigned as ‘clusters’ to one of the two intervention groups. A total of 18 clusters were randomized, which were equally divided in 9 clusters that were allocated to the limited intervention and 9 clusters that were allocated to the extensive intervention. In each of these clusters, one or more OPs were assigned to contribute to PerfectFit, based on shown interest. We chose for a cluster design to ensure that the OPs were only active within a single study arm. The organizational unit was the preferred cluster for two reasons. First, OPs from the same organizational unit were all trained to execute the intervention so that discussions among colleagues would not bias the results. Second, grouping participants from the same organizational unit into the same intervention group will prevent so-called “contamination effects” among participants, i.e., talking and sharing experiences about involvement in two different types of interventions, which might influence their behaviors [69, 70].

In the military force we constructed ten clusters consisting of military ground force army bases located in different regions in The Netherlands. Since the police force was facing a large reorganization with possible replacements of OPs from one organizational unit to another, only two clusters could be constructed, based on organizational units in different regions. Randomization in the academic hospital was performed at the ward level, creating a total of 6 clusters.

For all organizations, the OPs only perform work for the health center within that particular organizational unit. Clusters were ordered according to their sizes, i.e. the number of potential eligible participants. For each pair of clusters of similar size within one organization, one of the clusters was randomly allocated to the extensive intervention and the other to the limited intervention. Randomization took place after an OP from the unit had confirmed participation, and prior to the inclusion of individual participants. A researcher who was not otherwise involved in the trial used version 3.0.1 of The R Foundation for Statistical Computing for the randomization. Researchers, participating OPs, and participants were not blinded for the group allocation, since this was impossible given the nature of the intervention and the cluster design.

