## Results

### Baseline characteristics of participants

Figure 1 shows the CONSORT diagram [72] of the flow of clusters and participants through the first phases of the trial. In total, 9 clusters (*n* = 217), were assigned to the limited intervention (control), and 9 clusters (*n* = 274) to the extensive intervention (intervention). One cluster dropped out after randomization and before any cardio screenings were done, because the only OP within this cluster had other priorities in work. Three more OPs dropped out before any cardio screenings were done, two because of personal problems and one because she left her job. A total of 652 employees undertook the cardio screening. Based on these cardio screenings, 91.4 % (*n* = 598) were found to have risk factors for CVD, of whom 82.3 % were included (*n* = 493). Reasons for no inclusion were the presence of exclusion criteria or retirement or having to go abroad for work in the near future. For 16 participants the baseline questionnaire was missing, but we did receive blood- or anthropometric-measurements. The number of missings ranged from *n* = 1 (for the variable age) to *n* = 40 (for the variable level of education).

Baseline characteristics of participants in the three organizations are presented in Table 1. The military and police forces included a majority of males, whereas the hospital included mostly females. Among participants of the police force more than 76 % had a BMI higher than 25 kg/m2, and in the military force this percentage was 80.5 %. The percentage in the hospital of 46 % is lower and is similar to the average for the Dutch population.

Table 2 presents the baseline characteristics of the extensive intervention versus control study groups. The average age of the participants was 52, and 81.4 % were male. The randomization was successful in creating study groups with similar characteristics. Only for smoking a difference between the groups was found (*p* = 0.026). The CVD risk based on the Framingham score showed that more than 30 % of our study population is at intermediate or high risk, without differences in distribution between the two groups (*p* = 0.430).

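### The 220-per-group, 80% power basis assumes about 11 clusters of 20 per arm, which this trial does not have, and power was not restated after clusters and recruitment changed

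*Protocol article*

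**What the plan says.** The sample size section of the Protocol article assumes a mean general health score of 71 with SD 19 on a 0-100 scale, and a "difference in the general health score between the intervention and control groups after 12 months of 10 % in favor of the intervention group". The test is specified as "With a power of 80 %, a significance level of 5 %, two-tailed testing", with an "estimated intra-cluster correlation coefficient of 0.05". From these it concludes that "approximately 220 participants per group are needed to demonstrate a difference in treatment effect of 10 % between the two groups". With 50% participation and 30% loss to follow-up, it arrives at 634 invitations per arm. It gives no cluster size or cluster number with the 220.

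The randomization section describes 18 clusters, 9 per arm: ten military, two police and six hospital. For the police, "only two clusters could be constructed, based on organizational units in different regions". The baseline results report that "One cluster dropped out after randomization and before any cardio screenings were done", and that 217 and 274 people were included. The study design section says inclusions fell short, and gives the reason for adding the hospital: "In order to achieve sufficient power, we obtained approval of the METC to include an additional organization". No power figure for the revised design follows.

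**The concern.** The 220 already contains an allowance for clustering, and that allowance depends on cluster size. If the trial's clusters are fewer, larger or more unequal than the calculation assumed, 220 per group no longer gives 80% power. Fewer included people widens the gap.

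The article was written after inclusion had closed and prints the final cluster counts and numbers included. A reader who sees the 80% basis, the statement that an organization was added for power, and 491 participants may take the planned power as roughly in place. A null result on the primary outcome would then be read as evidence that motivational interviewing adds nothing, when the trial may have little better than even odds of detecting the planned effect.

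**Working it through.** **Inputs.** Mean 71, SD 19, ICC 0.05, 80% power, two-sided 5%, 30% loss and 50% participation come from the sample size section. Cluster counts come from the randomization section; paired allocation within organization gives 5 military, 1 police and 3 hospital clusters per arm before the loss of one military cluster. Participants by organization come from Table 2: limited arm 124 police, 60 military, 33 hospital (217); extensive arm 138, 110, 26 (274).

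**1. Reproducing 220.** 10% of 71 is 7.1 points. Individual randomization needs 2 × (1.96 + 0.8416)² × 19² / 7.1² = 112.4 per group. 220 / 112.4 = 1.957 = 1 + (m − 1) × 0.05, so m = 20.1 and 220 / 20.1 is about 11 clusters per arm. The t-based count is 114, and 114 × 1.95 = 222. Then 222 / (0.7 × 0.5) = 634, the stated number to invite. The sum is sound for clusters of 20.

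**2. The same target in nine equal clusters per arm.** 220 analysed per arm gives 76% (normal) or 70% (t). Reaching 80% (normal) would take about 284 per arm: 112.4 × 0.95 / (1 − 112.4 × 0.05 / 9).

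**3. Recruitment against the plan's chain.** 634 × 0.5 = 317 inclusions per arm were required; 217 and 274 were obtained. After 30% loss, 217 × 0.7 = 152 and 274 × 0.7 = 192 remain. The limited arm is below 220 before any loss.

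**4. Actual clusters.** Effective size per arm is the sum over clusters of m / (1 + (m − 1) × 0.05), with the 30% loss applied to each m first. With all 18 clusters:

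| Cluster type | Limited: m after loss, effective size | Extensive: m after loss, effective size |
|---|---|---|
| Police (1) | 86.8, 16.4 | 96.6, 16.7 |
| Military (5 equal) | 8.4 each, 5 × 6.13 = 30.7 | 15.4 each, 5 × 8.95 = 44.8 |
| Hospital (3 equal) | 7.7 each, 3 × 5.77 = 17.3 | 6.07 each, 3 × 4.84 = 14.5 |
| Total | 64.4 | 76.0 |

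The police clusters have design effects of 5.3 and 5.8, so each is worth fewer than 17 independent people. The arm of the lost military cluster is not stated. Removing it from the limited arm gives 62.2 and 76.0; from the extensive arm, 64.4 and 71.5. All compare with 112.4 needed.

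**5. Power for 7.1 points.** SE = 19 × √(1/64.4 + 1/76.0) = 3.22, rising to 3.27 with 17 clusters.
- Normal: Φ(7.1 / SE − 1.96) = 58-60%.
- Noncentral t with 15-16 df: 53-55%.
- Difference detectable at 80% power: 2.80 × SE = 9.0-9.2 points (normal), 9.6-9.8 (t).
- No loss at all: 66-68% (normal), 60-62% (t).

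**6. The hospital's contribution.** Without it the 18-cluster totals fall to 47.1 and 61.5, SE is 3.68 and normal power is 49% (about 48% with the lost cluster removed). With it, power is about 59%.

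**7. Sensitivity, 30% loss.** At ICC 0.01 power is about 82% (normal) or 77% (t); at 0.02, 74% or 68%; at 0.10, 45% or 40%.

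**8. Baseline adjustment.** No correlation is given, so values are assumed. If adjustment multiplies the SE by √(1 − r²), r = 0.5 gives 3.22 × 0.866 = 2.79 and up to 72% (normal). r = 0.6 gives 3.22 × 0.8 = 2.58 and just under 80%. r = 0.7 gives up to 87%.

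**The case against.** **A reader might infer that 220 is an arithmetic error.** It is not. It reproduces for clusters of about 20, and the invitation count follows from it. The mismatch is with the trial's structure.

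**A reader might infer that the article claims 80% power was achieved, or that the hospital restored it.** The text supports neither. The sample size section says what was needed, and the hospital sentence states a purpose. The article openly reports the lost cluster and the low inclusion. What is absent is any statement of whether the revised design still meets its target.

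**A reader might take 53-60% as the trial's power.** That range is the unadjusted 12-month comparison. The article plans mixed models on repeated measurements with covariates, with general health measured at 0, 6 and 12 months, so true power could be higher. Reaching 80% (normal) needs a baseline correlation above about 0.6 if both variance components shrink together. If only individual-level variance falls, the gain is smaller: about 65% at r = 0.5 and 72% at r = 0.7 at the lower end. Pairing by organization and size may also reduce between-cluster variance. This objection stands against a firm figure. It does not rescue the printed basis, which claims no such gain.

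**10% could mean 10 scale points.** Power would then be 82-87% and the conclusion would reverse. But individual randomization would need 56.7 per group, so 220 implies a design effect of 3.88, about 59 per cluster and fewer than four clusters per arm. Eleven per arm is not the randomized design either, but it rests on a round cluster size of 20 that also leads to 634. The 7.1-point reading is therefore the more natural one, though not certain.

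**Conclusion.** The concern holds: the printed sample size basis does not fit the trial the same article describes. The implied cluster structure (about 11 clusters of 20 per arm) is not the randomized one, about half of each arm sits in one police cluster, and inclusion is 100 and 43 short of the 317 per arm required. The structural mismatch and the inclusion shortfall rest on printed figures and the 7.1-point reading; the shortfall itself does not depend on that reading.

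The power figure is conditional. At ICC 0.05 with 30% loss it is about 58-60% (normal) or 53-55% (t), with a detectable difference of 9.0-9.8 points, about 13-14% of 71. This assumes 7.1 points, uniform loss, equal military and ward sizes within each arm, and no baseline adjustment. Unequal military or ward sizes would lower it, while a smaller ICC or useful baseline correlation would raise it. Adding the hospital was a real gain, but on these assumptions power stays well short of 80%.

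**What to change.** Keep the existing calculation as the planning basis. State the cluster size behind it (about 20) and that 10% means 7.1 points; if 10 points was meant, say so and correct the derivation of 220.

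Add a restated power and minimum detectable difference for the trial as it stands, using:
- the actual sizes of the 17 active clusters and a design effect for unequal sizes;
- ICC 0.05, with a range of 0.01 to 0.10;
- 30% loss applied to cluster sizes before the design effect;
- cluster-level degrees of freedom;
- any gain from baseline adjustment shown separately, with the assumed correlation stated.

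Say that adding the hospital raised power (from about 48% to about 59%, normal, unadjusted) without restoring the planned 80%.

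The cost is text and a short calculation. No extra participants are needed. The only downside is a less favourable stated power.
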